### Intervention

#### Experimental group

Patients in the phase I and phase II experimental arms will be treated with concomitant TMZ radio-chemotherapy (STUPP protocol) in combination with AGuIX nanoparticles during the concomitant radio-chemotherapy period (Fig. 1).

**Fig. 1 Fig1:**
[figure not shown]
Overview of the treatment period of the NANO-GBM study

Nanoparticles AGuIX (experimental treatment) provided by NH TherAguix, will be administered in 4 intravenous injections. The first one will be administered 3 to 7 days before the start of the radio-chemotherapy and at least 48 h after dosimetry MRI. The next three injections will be administered during the radio-chemotherapy at the first day of the week 1, week 2 and week 3. The injection will be performed 4 h (± 1 h) before RT and 3 h before TMZ. For phase I, the dose administered at each injection will be 50, or 75 or 100 mg/kg (tested doses). For phase II, the dose administered at each injection will be the dose recommended after phase I.

#### Control group

Patients in the phase II reference arm will be treated with the standard STUPP protocol: RT at a dose of 60 Gy (30 fractions/6 weeks) and concomitant treatment with daily oral TMZ (75 mg/m^2^/day) from the first day of RT until the end of RT. Then, adjuvant TMZ will be reintroduced 4 weeks after the end of RT according to a 5-days schedule every 28 days (150 mg/m^2^/day for the first cycle and then at 200 mg/m^2^/day in the absence of toxicity).

### Study procedures and participant timeline

The overview of study assessments and procedures is presented in Table 2**.**

**Table 2 Tab2:** Data collection schedule

	**Screening / inclusion**		**Concomitant chemoradiotherapy phase**						**Therapeutic break**				**Adjuvant phase**							
Timepoint													**cycle 1**				**cycle 2**			
Week		**W0**	**W1**	**W2**	**W3**	**W4**	**W5**	**W6**	**W7**	**W8**	**W9**	**W10**	**W11**	**W12**	**W1 3**	**W1 4**	**W1 5**	**W16**	**W1 7**	**W18**
Day	**(-28 à -7)**	**at -7 to -3**	**0**	**7**	**14**	**21**	**28**	**35**	**42**	**49**	**56**	**63**	**70 ± 4d**	**77**	**84**	**91**	**98 ± 4d**	**105**	**112**	**119**
Informed consent	✓																			
Medical history and demographics	✓																			
Initial histology / centralized review (FFPE tumor block)	✓																			
Previous/concomitant treatments (including corticosteroids)	✓		throughout the treatment																	
Evaluation of adverse events			throughout the treatment																	
Radiological evaluation MRI (disease)	✓(according to standard practice)												✓							
MRI dosimetry	✓(-15 à -5)																			
MRI post injection AGuIX (1 h after injection)^h^		✓^**h**^			✓^**h**^															
Examination neurological (MMSE)	✓												✓							
Clinical examination, weight	✓	✓^**h**^	✓	✓	✓	✓	✓	✓					✓				✓			
Vital signs^a^	✓	✓^**h**^	✓	✓	✓	✓	✓	✓					✓				✓			
KPS Performance Index	✓	✓^**h**^	✓	✓	✓	✓	✓	✓					✓				✓			
Serum pregnancy test^g^	✓				✓			✓					✓				✓			
Hematology^b^	✓	✓^**h**^	✓	✓	✓	✓	✓	✓					✓				✓			
Fasting biochemistry^c^	✓	✓^**h**^	✓	✓	✓	✓	✓	✓					✓				✓			
Urine analysis^d^	✓	✓^**h**^	✓	✓	✓	✓	✓	✓					✓				✓			
Pharmacokinetics^f^			✓^f^	✓^f^	✓^f^															
Radiotherapy			**2 Gy**** x 5d / week pour 6 weeks**																	
Temozolomide			**75 mg/m**^**2**^** daily intake D0 à D42**										**5D**^**e**^				**5D**^**e**^			
AGuIX (injection IV)^i^		**D-7 to D- 3**^**j,h**^	**D0**^**h**^	**D7**^**h**^	**D14**^**h**^															
survival assessment			throughout the study																	

	**Adjuvant phase**																**End of treatment visit**	**Follow-up to progression**	**Follow-up of survival**
Timepoint	**cycle 3**				**cycle 4**				**cycle 5**				**cycle 6**					**every 3 months for 18 months after V(W35) then every 6 months**	**every 3 months for 18 months after V(W35) then every 6 months**
Week	**W19**	**W20**	**W21**	**W22**	**W23**	**W24**	**W25**	**W26**	**W27**	**W28**	**W29**	**W30**	**W31**	**W32**	**W33**	**W34**	**W35**		
Day	**126 ± 4d**	**133**	**140**	**147**	**154 ± 4d**	**161**	**168**	**175**	**182 ± 4d**	**189**	**196**	**203**	**210 ± 4d**	**217**	**224**	**231**			
Informed consent																			
Medical history and demographics																			
Initial histology / centralized review (FFPE tumor block)																			
Previous/concomitant treatments (including corticosteroids)																			
Evaluation of adverse events																			
Radiological evaluation MRI (disease)					✓												✓	✓	
MRI dosimetry																			
MRI post injection AGuIX (1 h after injection)^h^																			
Examination neurological (MMSE)					✓												✓	✓	
Clinical examination, weight	✓				✓				✓				✓				✓	✓	
Vital signs^a^	✓				✓				✓				✓				✓		
KPS Performance Index	✓				✓				✓				✓				✓	✓	
Serum pregnancy test^g^	✓				✓				✓										
Hematology^b^	✓				✓				✓				✓				✓		
Fasting biochemistry^c^	✓				✓				✓				✓				✓		
Urine analysis^d^	✓				✓				✓				✓				✓		
Pharmacokinetics^f^																			
Radiotherapy																			
Temozolomide	**5D**^**e**^				**5D**^**e**^				**5D**^**e**^				**5D**^**e**^						
AGuIX (injection IV)^i^																			
survival assessment																			✓

^a^vital signs include heart rate measurement, systolic and diastolic blood pressure, temperature, pulse

^b^hemoglobin, CBC platelet

^c^glucose, sodium, potassium, magnesium, calcium, total protein, creatinine, urea, AST, ALT, alkaline phosphatase, GGT, total bilirubin

^d^proteinuria

^e^TMZ 150—200 mg/m^2^/d D1 at D5 every 28 days (the daily dose of 150 mg/m^2^ for the first cycle will be increased to 200 mg/m^2^ for the 2nd cycle in the absence of significant toxicity)

^f^pharmacokinetics performed only for phase I patients: blood sampling 7 ml before injection, 15 min, 30 min, 1 h (before MRI), 2 h, 3 h, 4 h (before the beginning of radiotherapy), 6 h and 24 h post injection + urine collection during 6 h

^g^for patients of childbearing age

^h^only for patients receiving the experimental treatment: Phase I + Phase II experimental arm

^i^experimental treatment: for phase I patients (dose of 50 or 75 or 100 mg/kg according to the TITE CRM) and for patients in the experimental arm of phase II (at the dose recommended by phase I) At S1J0, S2J7 and S3J14 the injection will be performed 4 h ± 1 h before the radiotherapy session

^j^injection performed 3 to 7 days before the start of radiochemotherapy, and at least 2 days after the MRI dosimetry

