### Participant eligibility

The inclusion and non-inclusion criteria are presented in Table 1.

**Table 1 Tab1:** Section criteria

Inclusion criteria	Non-inclusion criteria
Histological diagnosis of grade IV glioblastoma (biopsy or partial surgery)	History of cerebral radiotherapy
Patient not operated or in partial excision	History of chemotherapy (including carmustine (Gliadel®) implants) or immunotherapy (including vaccination)
Karnofsky performance status ≥ 70%	Any contraindication to TMZ listed in the multidisciplinary consultation meeting
Age ≥ 18 years and < 75 years	History of major bowel resection that may affect oral drug absorption in the judgment of the investigator
Life expectancy ≥ 6 months	Diagnosed inflammatory bowel disease (Crohn's disease or ulcerative colitis)
Platelets ≥ 100 000/mm^3^	Diarrhea ≥ CTCAE grade 2 (regardless of cause)
PNN ≥ 2000/mm^3^	Current or recent treatment with another investigational drug or participation in another therapeutic clinical trial (within 30 days of inclusion)
Hemoglobin ≥ 10 g/dL	History of other cancer within 5 years prior to inclusion except basal cell carcinoma of the skin and carcinoma in situ of the cervix
Creatinine < 1.5 times the upper normal limit or Cockcroft-Gault clearance ≥ 50 mL/min	Pregnant or breastfeeding women
Liver function (GGT, PAL, AST, ALT, bilirubin) < 1.5 times the upper normal limit	Contraindication to MRI or gadolinium injection
For patients receiving corticosteroid therapy, corticosteroid therapy must be at a stable or decreasing dose for at least 14 days prior to inclusion	History of severe anaphylactic reactions due to the injection of gadolinium-based contrast material (Dotarem®, etc.)
Patient able to swallow and maintain oral therapy	Patient under guardianship or curatorship
Negative serum pregnancy test within 7 days prior to first administration of therapy for women	History of nephropathy
Women of childbearing potential and men whose partners are of childbearing potential must agree to use an approved method of contraception for themselves or their partners for the duration of treatment and at least 6 months after the last study treatment	Psychological disorder or social or geographical reasons that could compromise the medical follow-up of the trial or compliance with the treatment
Obtaining signed informed consent from the patient	
Patient enrolled in a social security plan	

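### Table 2 schedules a serum pregnancy test at the start of adjuvant temozolomide cycles 1 to 5 but not at cycle 6, with no stated reason

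*Protocol article*

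**What the plan says.** Table 2 (Study procedures and participant timeline) sets out the visits week by week in two parts.

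- **Pregnancy test.** The row "Serum pregnancy test^g" is ticked at screening, W3, W6, W11 and W15 in the first part, and at W19, W23 and W27 in the second. Its cells at W31 and at the end-of-treatment visit (W35) are empty. Footnote g says who is tested, "for patients of childbearing age", and makes no exception by cycle or by arm.
- **Temozolomide.** A 5-day course is entered at W11, W15, W19, W23, W27 and W31. Footnote e describes it as "TMZ 150—200 mg/m^2^/d D1 at D5 every 28 days", and the Control group section likewise has adjuvant treatment given "according to a 5-days schedule every 28 days".
- **Items tied to AGuIX.** These carry footnote h, "only for patients receiving the experimental treatment: Phase I + Phase II experimental arm". The pregnancy-test row does not carry it.
- **Contraception.** Table 1 requires it "for the duration of treatment and at least 6 months after the last study treatment".

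**The concern.** The adjuvant phase consists of six courses of one drug on one schedule. The pregnancy test accompanies the first five and then stops, although nothing in the article makes cycle 6 different. The contraception requirement in Table 1 shows that the protocol still regards pregnancy as a risk at that time.

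A site working from the table would give the last course without a test planned for that visit. W35 is blank too, so no pregnancy test is scheduled at all after the one at cycle 5. What is at stake is a safety check in a small group of patients. The sample size, the endpoints and the analysis are untouched.

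**Working it through.** The check is a column count of Table 2 followed by simple date arithmetic. The plan gives no figure to reproduce.

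**Step 1: rows side by side at the six adjuvant cycle starts**

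| Cycle | Week | Day | Temozolomide course | Six other safety rows* | Pregnancy test |
|---|---|---|---|---|---|
| 1 | W11 | 70 ± 4 | yes | all ticked | ticked |
| 2 | W15 | 98 ± 4 | yes | all ticked | ticked |
| 3 | W19 | 126 ± 4 | yes | all ticked | ticked |
| 4 | W23 | 154 ± 4 | yes | all ticked | ticked |
| 5 | W27 | 182 ± 4 | yes | all ticked | ticked |
| 6 | W31 | 210 ± 4 | yes | all ticked | **blank** |

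*Clinical examination, vital signs, performance status, haematology, biochemistry, urine analysis.

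Totals: temozolomide 6 of 6; other safety rows 6 × 6 = 36 of 36 cells; pregnancy test 5 of 6.

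**Step 2: could the blank come from a shifted column?** The second part of the table has 19 columns: W19 to W34 (columns 1 to 16), W35 (17) and two follow-up columns (18 and 19). The pregnancy-test row has all 19 cells, with ticks in columns 1, 5 and 9. Vital signs, haematology, biochemistry and urine analysis are ticked in columns 1, 5, 9, 13 and 17, and temozolomide is entered in columns 1, 5, 9 and 13. The pregnancy-test ticks therefore line up with the neighbouring rows, and only column 13 (W31) departs from the cycle-start pattern. A shift would have moved the other ticks as well.

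**Step 3: could the stop be tied to AGuIX?** One might suppose that testing ends about six months after the last AGuIX injection on D14. The footnotes do not support this. Procedures confined to AGuIX recipients are marked h, whereas this row is marked g only. It therefore also covers the reference arm, which never receives AGuIX.

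**Step 4: age of the most recent scheduled test when cycle 6 starts**

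- Nominal: 210 − 182 = 28 days.
- Shortest, with the ± 4-day windows: (210 − 4) − (182 + 4) = 206 − 186 = 20 days.
- Longest: (210 + 4) − (182 − 4) = 214 − 178 = 36 days.

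At cycles 1 to 5 the test falls in the same week as the course.

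**The case against.** The strongest reply is that the blank breaks no rule. Footnote g only says who is tested, footnote e only sets the dosing, and Table 1 asks for a negative test before first administration and for contraception. None of these calls for a test at every cycle. That is correct, and the point is limited to an unexplained break in the table's own pattern.

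A second reply is that this row never followed the other safety rows. During chemoradiotherapy those rows are ticked weekly from W1 to W6, while the pregnancy test is ticked only at W3 and W6. The schedule already accepts gaps of 35 − 14 = 21 days (W3 to W6) and 70 − 35 = 35 days (W6 to W11), so 28 days is not unusual in itself. This also stands. It does not explain why, within the adjuvant phase, five starts of the same course have a same-week test and the sixth does not.

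A third reply is that W35 is blank as well, so the sponsor may have decided to end testing after cycle 5. That is possible, but the article does not say so, and one course remains to be given at that point.

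Finally, the article condenses a fuller protocol, and its table was extracted from a PDF by a program. The intact cell count makes a shift unlikely, but the loss of a single tick cannot be fully excluded. Condensation is a weaker explanation, because the article did not leave the testing schedule to the full protocol: it printed it visit by visit.

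**Conclusion.** The point holds at the lowest severity. As printed, one of the six adjuvant temozolomide courses starts without the same-week pregnancy test scheduled for the other five, and the latest scheduled result is then 28 days old (range 20 to 36). It affects only women of childbearing age who reach cycle 6. The article gives no count of them; the ceiling is the 66 patients in the whole trial, and the real number is likely to be very small. No endpoint, error rate or analysis changes.

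The conclusion assumes that the table has been read correctly at W31 and that no exemption stands in the full protocol. Confidence is moderate for those two reasons.

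**What to change.** Tick the serum pregnancy test at W31 in Table 2. Blood is already drawn at that visit for haematology and biochemistry, so the cost is one table cell and one extra assay in a few patients. If cycle 6 is meant to be exempt, say so in a footnote with the reason; the same note could state whether the blank at W35 is intended. If the full protocol already has the W31 tick, only the published table needs correcting.

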### Statistical analysis

#### Sample size

A maximum of 12 patients will be treated in phase I (sample size obtained by simulation, and in agreement with the bound obtained by Cheung’s formula, 2013), minimum 6 patients to be treated at the recommended dose, who will then be included and analyzed in phase II.

The phase II trial consists of a randomized study with a 2:1 ratio in favor of the experimental arm. For the experimental arm, a single-stage Fleming design will be used, based on an acceptable success rate of 70% and a 50% unacceptable success rate. In order to limit the one-sided alpha risk (of wrongly concluding that the treatment is effective) to 5% and the beta risk (of wrongly failing to conclude that the treatment is effective) to 20%, the minimum number of patients to include is 37. The treatment will be considered effective (and therefore the phase II positive) as soon as 24 successes out of 37 are obtained. In this case, the estimate of the probability of success will be of around 65%, with a 90% confidence interval (90% CI) of 51.4%-76.7% (Jeffreys interval).

It was decided to include 40 patients in the experimental arm, to compensate for a rate of about 10% of missing data (all reasons combined). Therefore, the number of patients in the reference arm will be 20.

Consequently, the total number of patients to be included is 66 (maximum): 12 patients in phase I, of which (minimum) 6 were treated at the recommended dose, 34 additional patients in the experimental arm of phase II, and 20 patients in the reference arm of phase II.

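### The phase II success cut-off is printed only for 37 patients although 40 are enrolled, and 40 patients cover a 7.5% loss, not the stated 10%

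*Protocol article*

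**What the plan says.** The Sample size section of the protocol article plans the experimental arm as a one-stage Fleming test. The rates it rests on are given there: "based on an acceptable success rate of 70% and a 50% unacceptable success rate". One-sided alpha is 5% and beta is 20%. From these it concludes that "the minimum number of patients to include is 37", and gives the decision rule: "The treatment will be considered effective (and therefore the phase II positive) as soon as 24 successes out of 37 are obtained". The next paragraph raises the enrolment: "It was decided to include 40 patients in the experimental arm, to compensate for a rate of about 10% of missing data". The 40 are made up of at least 6 phase I patients treated at the recommended dose plus 34 further patients.

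The Data analysis section defines the analysis population as patients with at least one AGuIX injection and says that missing data are not replaced. It estimates progression-free survival by Kaplan–Meier, and reports the 6-month rate in the experimental arm with a 90% confidence interval, read by the Fleming method. It gives no second cut-off and does not limit the analysis to 37 patients.

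**The concern.** A Fleming cut-off belongs to one sample size. The article prints a cut-off for 37 and an enrolment of 40, and nothing in it links the two. If losses are lighter than planned, 38 to 40 patients will be analysed and the only printed count will be 24. Applying it there would admit a treatment at the unacceptable 50% rate more often than the stated 5%. If losses match the plan, fewer than 37 will probably be analysed and the stated 80% power is not reached.

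This rule is the only go/no-go criterion for efficacy in phase II. The trial is open-label and makes no formal comparison with the reference arm. A cut-off chosen once the number analysed, and perhaps the results, are known would be a post hoc decision.

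**Working it through.** **Inputs (Sample size section).** Unacceptable rate p0 = 0.50; acceptable rate p1 = 0.70; one-sided alpha 0.05; power 0.80; n = 37; cut-off r = 24; enrolment 40; loss about 10%.

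**Formulas.** With X binomial(n, p): alpha = P(X ≥ r | n, 0.50) and power = P(X ≥ r | n, 0.70).

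**Step 1: the plan's own figures.** At n = 37, r = 24, alpha = 0.0494 and power = 0.8071. A search over n from 25 to 49 shows that 37 is the smallest n meeting both limits. The Jeffreys 90% interval for 24/37 is 51.4% to 76.6%, against 51.4% to 76.7% in the article. The design for 37 patients is correct.

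**Step 2: keep 24 and change n.**

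| n | alpha with r = 24 | Jeffreys 90% lower limit for 24/n |
|---|---|---|
| 37 | 4.9% | 51.4% |
| 38 | 7.2% | 49.9% |
| 39 | 10.0% | 48.4% |
| 40 | 13.4% | 47.0% |

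From 38 upwards alpha exceeds 5% and the interval includes the unacceptable 50%. A fixed count of 24 and the interval would then point in different directions.

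**Step 3: smallest cut-off with exact alpha ≤ 5% at each n.**

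| n | r | alpha | power |
|---|---|---|---|
| 35 | 23 | 4.5% | 77.3% |
| 36 | 24 | 3.3% | 73.7% |
| 37 | 24 | 4.9% | 80.7% |
| 38 | 25 | 3.7% | 77.5% |
| 39 | 26 | 2.7% | 74.0% |
| 40 | 26 | 4.0% | 80.7% |

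Between 35 and 40, only 37 and 40 meet both limits. At n = 36, lowering r to 23 gives power 83.7% but alpha 6.6%, so no cut-off there meets both.

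**Step 4: the loss allowance.** 40 × (1 − 0.10) = 36, one below the stated minimum. The loss that leaves 37 is 1 − 37/40 = 7.5%. To expect 37 after a 10% loss needs 37/0.90 = 41.1, that is 42 patients.

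**Step 5: average over random loss.** Assume that each of the 40 patients is lost independently with probability 0.10 (a modelling assumption, not in the article). Then P(fewer than 37) = 57.7%, P(exactly 37) = 20.0% and P(38 or more) = 22.3%; these sum to 100%. P(35 or fewer) is about 37%. With the alpha-valid cut-off at each n, average alpha is 3.8% and average power 75.5%. If 24 were kept at every n, average alpha would be 4.1% and average power 71.4%.

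**The case against.** The strongest reply is that the article never says 24 is used with any denominator but 37. It ties the count to its denominator and reads the result by the Fleming method, which supports recomputing the cut-off at the number analysed. Reading the rule as a proportion leads to the same place: 24/37 = 64.9%, which gives 24.6, 25.3 and 25.9 at n = 38, 39 and 40, so 25, 26 and 26 after rounding up. Those are the alpha-valid cut-offs. Moreover, under the plan's own 10% loss taken as random, even a fixed 24 gives an average alpha of about 4.1%, and the 13.4% arises only with no loss at all (probability 0.90^40 = 1.5%). All of this stands. A reader might infer that the plan breaks its 5% alpha; the document does not support that. What is left is that the number which decides phase II is printed for one sample size and a different size is enrolled.

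A reader might also take the words *as soon as* to mean that success can be declared the moment the 24th success is seen. The design is single-stage and no efficacy look is described; the review after 20 treated patients is there to confirm the recommended dose. The phrase is loose wording, not a sequential rule.

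On power, the allowance is only approximate, a loss of 3 in 40 leaves exactly 37, and 40 against 42 is a small gap. Part of the shortfall is binomial discreteness, since power also drops below 80% at 38 and 39. That weakens the power half without removing it: at the stated 10%, the plan falls below its own minimum.

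Finally, a full protocol or analysis plan that is not shown may hold cut-offs for other sizes. Its absence here is not the complaint. The article itself publishes a threshold, an enrolment and a loss allowance that do not fit together.

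**Conclusion.** The point holds as a mismatch between three published figures and should be fixed. The 37-patient design is correct. Type I error is at risk only if 24 is carried over to 38, 39 or 40 patients, where it would be 7.2%, 10.0% or 13.4%; the article neither says this nor rules it out. The power shortfall does not depend on that reading. At a literal 10% loss, power is 73.7% with 36 patients, and under independent random loss it averages about 76% with alpha-valid cut-offs. If the loss is 7.5%, exactly 37 remain and the stated power is met.

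These figures assume that the decision is made on a count of successes among the patients analysed, with exact binomial tails at 50% and 70%.

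**What to change.** 1. Replace the single cut-off by a rule: the treatment is considered effective if at least r successes are observed, where r is the smallest count with exact one-sided alpha of at most 5% at a true rate of 50% for the number of patients analysed. Give examples: 35 patients, 23; 36, 24; 37, 24; 38, 25; 39, 26; 40, 26. The general rule matters more than the table, because under 10% random loss there is about a 37% chance of 35 or fewer patients. It would also cover an arm above 40, should more than the minimum of 6 phase I patients contribute.
2. Change *as soon as* to *if at least*.
3. State either that 40 patients cover about 7.5% missing data, or that power at 10% loss is about 74% to 76%.

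The cost is a few lines of text and a slightly less favourable power statement. No extra patients are needed and the conduct of the trial does not change. The rule should be fixed before the phase II outcome data are examined.
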